# Ethical Aspects

## Accordance with the regulations in force

The study will be governed at all times by the ethical principles contained in the Declaration of Helsinki and subsequent amendments.

See at: http://www.wma.net/en/30publications/10policies/b3/index.html.

The study will be governed by the principles of Good Clinical Practice (ICH Tripartite and Harmonised Guidelines for Good Clinical Practice) and therefore following the appropriate standard operating procedures.

Prior to the start of any study procedure, approval by the Clinical Research Ethics Committees of the 3 hospitals participating in the study is required.

## Benefit-risk assessment for subjects participating in the study.

Participants undergoing conventional rehabilitation and tele-rehabilitation perform a symptom-limited exercise stress test before starting physical exercise. In patients at low risk, such as the participants in this study, or even moderate risk, a symptom-limited exercise stress test is not considered imperative beforehand. In the present protocol, the stress test serves not to stratify the risk, which in principle is low in itself, but to establish the training heart rate and to serve as a comparator between groups for the functional capacity achieved after the rehabilitation program. In addition, it adds a safety factor for patients entering the two programs being evaluated.

The recommendations of the guidelines of the main Scientific Societies on equipment for the Rehabilitation Unit are followed, with personnel trained in CPR, a semi-automatic defibrillator, a crash cart and an outlet for supplying supplementary oxygen. Each hospital also has a protocol for action in the event of an emergency. Healthcare personnel are trained in the identification of symptoms of discomfort and in the use of the Börg scales. Prior to the start of each exercise session, an assessment of the patient's general condition is required, including: presence of cardiac symptoms, measurement of blood pressure, advice on medication compliance, and heart rate. Possible incidents suffered by each patient in the home activity program are also discussed.

Compared to the minimal risks of these programs, the benefit achieved in terms of reduced morbidity and mortality suggests that cardiac rehabilitation should be extended to the vast majority of patients who suffer an acute coronary event. This protocol is in fact a step forward, not only in the promotion of this new service to be offered by the Hospital Arnau de Vilanova, but also an attempt to expand, if the tele-rehabilitation strategy proves to be superior, the number of subjects who could have access to these programs.

## Information and informed consent sheet.

The study investigator shall explain to patients (or their legally authorised representatives) the nature of the study, its purposes, procedures, estimated duration, potential risks and expected benefits. It will be clearly stated that participation is voluntary and that they may withdraw from the study at any time and without detriment to their future health care. Before signing, you should read the contents and comment or ask any questions you may have. Two documents shall be signed and kept by the patient and the investigator. No procedure will be carried out unless this consent form has been signed.

## Data confidentiality

1. Regarding Investigators and personnel who have access to study procedures and data

Information provided by the Sponsor (or by any company/institution acting on its behalf), or produced during the clinical trial, including, but not limited to, the protocol, DCL, Investigator's Brochure, and results obtained during the course of the trial, will be considered confidential prior to publication of the results. The Investigator and any person under his/her authority agree to maintain the confidentiality of such information and not to share it with anyone without the prior written consent of the Sponsor.

However, the submission of this protocol and other documentation required by the IRB/IEC is expressly permitted, and IRB/IEC members are subject to the same obligations of confidentiality.

The Sub-Investigators shall be subject to the same obligations as the Investigator. The Investigator should inform the Sub-Investigators of the confidential nature of the clinical trial. The Investigator and the Sub-Investigators shall use the information provided only for the purposes specified in the clinical trial, excluding any personal use or use on behalf of a third party.

In addition, the Investigator and the Sponsor agree to adhere to the principles of confidentiality of personal data in relation to the patients, the Investigator, and the collaborators involved in the study.

1. Regarding the patients

The confidentiality of each patient's data will be respected at all times. The affiliation of each of the patients and their association with the study and, thus, access to the data collected in the DCL is ensured by a document to which only the investigators, monitors and health authorities, if applicable, have access. The DCLs contain only the identification number of each subject included. The data obtained will be handled in accordance with the Spanish regulations on the handling of computerised data (LO 15/1999, of 13 December on the protection of personal data).

## Interference with individual doctor's prescribing habits

The use of drugs is not evaluated in this study. The drugs prescribed at discharge from hospital can be modified by the various physicians doing the clinical follow-up with the aim of achieving optimal care for each pathology or improvement of cardiovascular risk factors. At discharge, the appropriate statin will be prescribed at the appropriate dose to hypothetically achieve a lowering of LDL cholesterol below 70 mg/dl according to the percentage of LDL lowering recognised for each statin and dose. During the study there will be no dose modification except for LDL levels above 100 mg/dl at 4 months, in which case the patient will be withdrawn from the study, as this variable is one of the efficacy parameters evaluated within the new telemonitoring strategy. Obviously, the patient will patient will obviously remain in the telerehabilitation program, although his or her final data will not be evaluable.

## Responsibility of all study participants.

A. Researcher

a. Sign a commitment in which they acknowledge themselves as investigators of the study and affirm that they are aware of the protocol and any modifications to it, being in agreement with its contents.

b. Inform the research subjects and obtain their consent.

c. Collect and record data correctly and respond to audits if necessary.

d. Respect data confidentiality.

e. Facilitate monitoring visits.

f. Be accountable to the scientific and professional community for the objectives, basic methodology and significance of the results of the study.

g. Keep on file:

- Copy of the authorisations of the CEIC and of the competent Health Authorities.

- Copy of the identification sheet of the selected patients.

- The original consent forms.

- A copy of the protocol.

- A copy of the CRD sheets.

- Accounting and sample receipt documents.

- Any correspondence relating to the study

All documentation should be retained for 15 years after the date of the final report. The responsibility for storage may be delegated to the sponsor by means of a certified statement. In such a form the investigator should at least retain the sheets identifying the subjects participating in the trial and the informed consent.

B. Coordinator Researcher

a. Sign the protocol and any amendments thereto together with the promoter.

b. Co-responsible with the promoter for the elaboration of the monitoring and final reports.

c. Contribute to the dissemination of the results of the study together with the promoter.

1. Monitor

The monitors will attest to the accuracy of the information collected in the CRDs and should be provided with the facilities of the investigative team.

D. Promotor

a. Sign the protocol and any amendments to the protocol with the coordinating investigator.

b. Providing the investigators with the protocol

c. Submit the protocol to the IRB/IEC

d. Request authorisation from the Administration and submit the corresponding documentation.

e. Submit the follow-up and final reports in due time and form, as well as communicate the termination or interruption, if any, and its cause.

f. Deliver a copy of the protocol and attached documentation to the heads of the health care service providers where the protocol is to be implemented.

g. Apply quality control on the data to ensure that they are reliable.

h. Identify sources of funding for the study

i. Sign the contract with the appropriate entity.

j. Make the results of the study public, if possible by publication in a scientific journal.

## Clinical Research Ethics Committee (IRB)

The protocol, consent form and other accompanying information will be reviewed by the IRB/IEC of the hospital concerned. Any modifications other than administrative changes must be approved by the IRB/IEC.

Changes in study conduct without amendment are considered violations that may lead to disqualification of the site.

## Study budget

In accordance with Royal Decree 561/93, the study will not start until the Director of the Centre where the study is being carried out has given his approval. To this end, a contract will be signed which will establish the amount of financial compensation for both the research team and the Centre in terms of direct and indirect expenses, if applicable.

## Insurance policy

With respect to any direct or indirect liability caused by investigational products in connection with this clinical trial, Nabelia assumes legal responsibility on behalf of the investigator and co-workers for any harm caused to patients by the use of the ITS system. This is on the condition that the investigators and co-workers have followed the instructions in accordance with the protocol, that the trial products have been supplied by Nabelia, and that the principal investigator and co-workers conduct the trial in accordance with the Standards of Good Clinical Practice.

TSB Technologies is in contact with various insurance companies to take out civil liability insurance. Given that the procedures to which the patients are subjected are the same as those carried out in normal clinical practice in the cardiac rehabilitation programs, the AEMPS will be asked for exemption from contracting this insurance. In the event that the application is rejected, the insurance policy will be taken out, complying with the points specified in Royal Decree 56/1993 of 16 April 1993, published in the Official State Gazette of 13 May 1993.

# Final report and dissemination of results

## Monitoring and final reports

During the study and once it is completed, the corresponding reports will be sent to the Spanish Agency for Medicines and Health Products, in accordance with the regulations in force.

## Dissemination of results

The Scientific Coordinator of the study together with the sponsor will be responsible for the timely dissemination of the results through the usual scientific means. As a multicentre study, it is mandatory that the first publication is based on data obtained from all patients analysed in the study. Collaborating investigators must agree not to submit data on an individual basis or for a subgroup of sites prior to the first full publication by the sponsor.

The sponsor will review submissions for accuracy (avoiding possible discrepancies with information submitted to the Health Authorities), verify that confidential information is not inadvertently disclosed, and provide any additional supplementary information.

# ANNEXES

**Annex 1: Data collection notebook**

**Annex 2: Agreement of the Head of Service**

**Annex 3: Commitment of the principal investigator**

**Annex 4: Commitment of the collaborating investigator**

**Annex 5: Patient informed consent**

## ANEX 1.

**VISIT - 1 // PRESELECTION**

| Patient Initials |  | | |
| --- | --- | --- | --- |
| Patient identification Code (n) |  | | |
| Age (years) |  | Gender (M/F) |  |
| Date (DD-MM-YY) |  | | |

**PRESELECTION CRITERIA**

| Age < 72 years (Y/N) |  |
| --- | --- |
| NSTEACS, STEACS or unstable angina (Y/N) |  |

**EXCLUSION CRITERIA**

| Uncontrolled atrial or ventricular arrhythmias (Y/N) |  |
| --- | --- |
| Valvopathy of at least moderate grade (Y/N) |  |
| Heart failure NYHA 2/4 or above (Y/N) |  |
| Malignancy or major cardiovascular, pulmonary, renal or hepatic disease as judged by the investigator (Y/N) |  |
| Cerebrovascular disease, such as cerebral ischaemia, infarction, embolism or haemorrhage (Y/N) |  |
| Uncontrolled HTA Y/N) |  |
| Moderate pulmonary hypertension (Y/N) |  |
| Thrombophlebitis (Y/N) |  |
| Uncontrolled endocrine pathology (Y/N) |  |
| Limiting musculoskeletal pathology (Y/N) |  |
| Psychiatric pathology (Y/N) |  |
| Ventricular aneurysm (Y/N) |  |
| Ejection fraction less than 50%. (Y/N) |  |

| Accepts Stress Test (Y/N) |  |
| --- | --- |
| Accepts participation (Y/N) |  |

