## Exclusion Criteria

- Refusal of informed consent

- At the discretion of the investigator, primarily due to advanced biological age.

- Severe renal insufficiency (GFR < 30ml/min/1.73 m2).

- EF less than 50%.

- Hepatic insufficiency GOT >2 times normal value.

- Uncontrolled blood pressure (>140/90 mmHg).

- Uncontrolled heart failure.

- Dissecting aortic aneurysm.

- Uncontrolled ventricular tachycardia or other dangerous ventricular arrhythmias (multifocal ventricular activity).

- Aortic or mitral valve disease.

- Recent systemic or pulmonary embolism.

- Active or recent thrombophlebitis.

- Acute infectious diseases.

- Uncontrolled supraventricular arrhythmias or tachycardias.

- Repeated or frequent ventricular ectopic activity.

- Moderate pulmonary hypertension.

- Ventricular aneurysm

- Uncontrolled diabetes, thyrotoxicosis, myxoedema

- Hepatic or renal insufficiency and other metabolic insufficiencies.

- Conduction disorders such as: Complete AV block. Left bundle branch block. Wolf-Parkinson-White syndrome.

- Fixed rate pacemaker.

- Severe anaemia.

- Psychoneurotic disorders.

- Neuromuscular, musculoskeletal and arthritic disorders that may limit activity.

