## Definition of the study population: selection criteria

1. Inclusion Criteria

- Patients after uncomplicated acute coronary syndrome of both sexes.
- Completion of a maximal or symptom-limited exercise test without angina or electrical ischaemia.
- Age equal to or less than 72 years.

1. Exclusion Criteria

- Refusal of informed consent
- At the investigator's judgement, primarily due to advanced biological age.
- Severe renal insufficiency (GFR < 30ml/min/1.73 m2).
- EF less than 50%.
- Hepatic insufficiency (GOT >2 times normal value).
- Uncontrolled blood pressure (>140/90 mmHg).
- Uncontrolled heart failure.
- Dissecting aortic aneurysm.
- ventricular tachycardia or other dangerous ventricular arrhythmias that are not controlled (multifocal ventricular activity).
- Aortic or mitral valve disease.
- Recent systemic or pulmonary embolism.
- Active or recent thrombophlebitis.
- Acute infectious diseases.
- Uncontrolled supraventricular arrhythmias or tachycardias.
- Repeated or frequent ventricular ectopic activity.
- Moderate pulmonary hypertension.
- Ventricular aneurysm.
- Uncontrolled diabetes, thyrotoxicosis, myxoedema,
- Hepatic or renal failure and other metabolic insufficiencies.
- Conduction disorders such as: Complete AV block. Left bundle branch block. Wolf-Parkinson-White syndrome.
- Fixed rate pacing.
- Severe anaemia.
- Psychoneurotic disorders.
- Neuromuscular, musculoskeletal and arthritic disorders that may limit activity.

1. Withdrawal Criteria

- Withdrawal of consent to continue the study.
- At the investigator's discretion if appropriate for the patient.
- Need to modify lipid-lowering treatment.
- Unwillingness to continue the study or loss due to dropout.
- Clinical events.
- Other reasons at the discretion of the investigator.

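### The Annex 1 preselection checklist and the section 6.3 selection criteria contradict each other on age, valve disease and heart failure, and some section 6.3 exclusions have no item on the form

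*Protocol*

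**What the plan says.** Section 6.3 defines the study population; sections 1.13 and 1.14 of the summary give essentially the same list. Its age criterion is "Age equal to or less than 72 years". Its exclusions include "Aortic or mitral valve disease", "Uncontrolled heart failure" and "Conduction disorders such as: Complete AV block. Left bundle branch block. Wolf-Parkinson-White syndrome". They also include fixed-rate pacing, severe anaemia, acute infectious disease, recent embolism and dissecting aortic aneurysm, and they set numeric limits for GFR (below 30), GOT (more than twice normal) and blood pressure (above 140/90 mmHg).

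The data collection notebook in Annex 1 opens with a Visit -1 preselection page. Its age item is "Age < 72 years (Y/N". Its exclusion items include "Valvopathy of at least moderate grade (Y/N" and "Heart failure NYHA 2/4 or above (Y/N". One item covers malignancy together with major disease of the heart, lungs, kidneys or liver, left to the investigator's judgement. Another covers cerebrovascular disease.

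The Visit 0 page then records only the stress-test result and consent. Section 6.4 makes the stress test the first procedure after consent, 7 to 10 days after discharge. History, examination and laboratory data follow only if its result allows inclusion.

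**The concern.** Two parts of one protocol give different answers to the question of who may enter. The checklist comes before the stress test: it asks whether the patient accepts the test, and the next page records the result. If staff work from the form, the limits on the form are the ones applied. The stakes are who takes an early exercise test, who is randomised, and whether the population reported as meeting section 6.3 is the one recruited. Patients come from two hospitals (section 6.1), so two teams could in good faith work from different lists.

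**Working it through.** No arithmetic applies, and the plan states no figure on this point. The check sets the two lists side by side.

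**Limits that differ**

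| Criterion | Section 6.3 | Annex 1, Visit -1 | Patient treated differently |
| --- | --- | --- | --- |
| Age | 72 admitted | must be below 72 | aged exactly 72: admitted by 6.3, turned away by the form |
| Valve disease | aortic or mitral, any grade | any valve, moderate or worse | mild aortic or mitral disease: excluded by 6.3, passes the form |
| Heart failure | only if uncontrolled | NYHA class 2 upward | controlled, NYHA 2: admitted by 6.3, turned away by the form |

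A smaller difference of the same kind is thrombophlebitis. Section 6.3 restricts it to current or recent disease, while the form has no time limit.

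**Section 6.3 exclusions with no place on the form (2):** severe anaemia and acute infectious disease. No checklist item names or implies either.

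**Section 6.3 exclusions with no item of their own (4):** conduction disorders, fixed-rate pacing, recent systemic or pulmonary embolism, and dissecting aortic aneurysm. These could be recorded only under the judgement-based item for major organ disease. A cerebral embolism would also fit the cerebrovascular item.

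**Numeric limits lost (3):** GFR, GOT and blood pressure. The form has items that touch renal disease, hepatic disease and hypertension, but none carries a number.

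**Named on the form only (2):** cerebrovascular disease and malignancy.

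**Is the gap closed later on the form?** It is not. Visit 0 does not return to the exclusions. The Visit 1 blood panel includes creatinine but has no field for GOT or haemoglobin, and neither do the 4- and 10-month panels. The GOT and anaemia exclusions therefore cannot be verified from the laboratory fields of the notebook at any visit.

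**An overlap inside the protocol list.** Section 1.14 excludes GFR below 30 and, separately, "Hepatic or renal insufficiency and other metabolic insufficiencies"; section 6.3 has the same pair, with failure in place of insufficiency in the second. A patient with, say, a GFR of 45 passes the first and may fail the second. Copying the list onto the form unchanged would carry this ambiguity with it.

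**Agreement.** Ejection fraction below 50%, ventricular aneurysm and moderate pulmonary hypertension match in both places.

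**The case against.** The best defence is that section 6.3 governs and Annex 1 only records. Section 6.3 is headed as the definition of the study population, and the Annex 1 page is headed as preselection within a data collection notebook. Section 9.2 requires eligibility to be established before allocation, and section 11 has the monitor go over the criteria and follow inclusion. Nothing says that the form overrides section 6.3. This stands: a reader might infer that the checklist is the rule in force, and the document does not support that. It does not remove the contradiction, because Annex 1 is part of the protocol and no other eligibility form is shown.

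The second defence is that the judgement-based item for major organ disease fills the gaps. It fills some. A reader who counts six or more exclusions as wholly absent would overstate the case: conduction disorders, pacing, embolism and aneurysm could be entered there, and frequent ventricular ectopy can fall under the arrhythmia item. But that route depends on the investigator, does not reach anaemia or infection, and does not help with mild valve disease, for which a specific item points the other way.

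The third defence is that section 6.3 lets the investigator exclude by judgement, which might cover malignancy or cerebrovascular disease. It does so only in part, since that clause is aimed mainly at advanced biological age. It does not reconcile the age or heart failure limits.

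**Conclusion.** The contradiction is real and runs in both directions. Three limits differ, two exclusions have no item, four depend on a judgement-based item, three numeric limits are missing from the form, and two conditions are named only on the form. The practical consequence assumes that staff rely on the checklist. On that assumption, a patient with mild aortic or mitral valve disease or severe anaemia could reach the stress test against section 6.3, and a patient aged exactly 72 or with controlled NYHA 2 heart failure could be refused against it. How many patients this would affect cannot be derived from the document.

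Two further inferences are tempting and not supported. One is that the enrolled population would match neither list: staff using only the form enrol the form's population, and staff applying both enrol those who satisfy both. The other is that the treatment comparison is biased: eligibility precedes randomisation, so the mismatch falls on both arms alike. The issue is the enrolled population and the screening before exercise. Section 6.3 also gives no reason for any single criterion, so it should not be said that each omitted one was set for exercise safety.

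**What to change.** The sponsor should reconcile section 1.14, section 6.3 and the two Annex 1 preselection tables into one agreed list. Each differing criterion needs a decision: age, valve disease, heart failure, thrombophlebitis, cerebrovascular disease, malignancy, and the overlap between GFR below 30 and the general renal and hepatic exclusion. The choice of each clinical limit rests with the sponsor. The checklist should then be aligned so that every exclusion has an item, with the numeric limits shown wherever the agreed list has them.

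The cost is a form revision and small wording changes, with ethics committee approval where the change is more than administrative (section 13.7). It is somewhat higher if GOT, GFR and anaemia are to be checked before the stress test: section 6.4 now places laboratory data after it, and the notebook would need GOT and haemoglobin fields. Sample size and analysis methods are unaffected.
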